[9.1. Analysis Objectives and Endpoints 40](#_Toc415569594)

[9.1.1. Analysis Objectives 40](#_Toc415569595)

[9.1.2. Primary Endpoint 40](#_Toc415569596)

[9.1.3. Secondary Endpoints 41](#_Toc415569597)

[9.1.5. Other Endpoints of Interest 41](#_Toc415569599)

[9.2. Analysis Conventions 41](#_Toc415569600)

[9.4. Demographic Data and Baseline Characteristics 41](#_Toc415569603)

[9.5. Data Analysis 42](#_Toc415569604)

[9.5.1. Primary Analyses 42](#_Toc415569605)

9.5.2 Exploratory Analyses 44

[9.7. Sample Size 44](#_Toc415569612)

[10. RESPONSIBILITIES 45](#_Toc415569613)

[10.1. Investigator Responsibilities 45](#_Toc415569614)

[10.1.1. Good Clinical Practice 45](#_Toc415569615)

[10.1.2. Institutional Review Board (IRB)/Independent Ethics Committee (IEC) Approval 45](#_Toc415569616)

[10.1.3. Informed Consent 45](#_Toc415569617)

[10.1.4. Confidentiality 46](#_Toc415569618)

[10.1.5. Study Files and Retention of Records 46](#_Toc415569619)

[10.1.6. Case Report Forms 47](#_Toc415569620)

[10.1.7. Investigational Medicinal Product Accountability and Return 47](#_Toc415569621)

[10.1.8. Inspections 47](#_Toc415569622)

[10.1.9. Protocol Compliance 47](#_Toc415569623)

[10.2. Sponsor Responsibilities 47](#_Toc415569624)

[10.2.1. Protocol Modifications 47](#_Toc415569625)

[10.2.2. Study Report and Publications 48](#_Toc415569626)

[10.3. Joint Investigator/Sponsor Responsibilities 48](#_Toc415569627)

[10.3.1. Payment Reporting 48](#_Toc415569628)

[10.3.2. Access to Information for Monitoring 48](#_Toc415569629)

[10.3.3. Access to Information for Auditing or Inspections 48](#_Toc415569630)

[10.3.4. Study Discontinuation 48](#_Toc415569631)

[11. REFERENCES 49](#_Toc415569632)

[12. APPENDICES **Error! Bookmark not defined.**](#_Toc415569633)

[Appendix 1. Study Procedures Table **Error! Bookmark not defined.**](#_Toc430780176)

[Appendix 2. Estimating Severity Grade for Parameters Not Identified in the Grading Table 54](#_Toc430780178)5

LIST OF IN-TEXT TABLES

[Table 5‑1. Concomitant Medications Disallowed or to be used with Caution 24](#_Toc430780179)

PROTOCOL SYNOPSIS

San Francisco Department of Public Health

[name]

San Francisco CA 94102

| Study Title: | Pilot Treatment as Prevention for HCV Among Persons Who Actively Inject Drugs |
| --- | --- |
| IND Number: | N/A |
| Study Centers Planned: | 1 site in the United States |
| Number of Subjects Planned: | 30 subjects |
| Target Population: | Hepatitis C virus (HCV), Genotype 1 infected adults |
| Duration of Treatment: | Subjects will be treated for 8 weeks |
| Objectives: | The primary objectives of this study are as follows:   1. To assess the feasibility of treating persons who actively inject drugs (PWIDs) for HCV with Ledipasvir/Sofosbuvir Fixed-Dose Combination (LDV/SOF) by modified directly observed therapy (mDOT) versus unobserved dosing, with motivational interviewing (MI) adherence counseling, as measured by recruitment and retention rates, overall and by arm. 2. To evaluate the acceptability of mDOT versus unobserved dosing, with MI adherence counseling, among PWIDs treated with LDV/SOF, as determined by mDOT and MI participation rates, medication adherence rates and the proportion of subjects that complete therapy, overall and by arm. 3. To assess through in-depth, semi-structured qualitative interviews, the challenges required for mDOT and unobserved dosing, and identify key factors affecting treatment adherence to LDV/SOF for PWIDs.   The exploratory objectives of this study are as follows:   1. To assess end-of-treatment response and sustained virologic response (SVR), as determined by the proportion with undetectable HCV RNA at week 8 and post-treatment week 12, by arm. 2. To assess adherence to treatment by SOF metabolite levels, by arm, as needed based on SVR rates and medication adherence data. 3. To assess drug use behaviors before and after HCV treatment. 4. To assess HCV relapse and reinfection at post-treatment week 36 among participants achieving SVR. 5. To evaluate demographic, behavioral and HCV strain correlates of adherence and SVR. 6. To characterize the social and injector networks of participants in preparation for a subsequent full TasP trial. |
| Study Design: | Thirty subjects will be enrolled 2-to-1 in one of the following two treatment arms:  **Group 1:** Modified Directly Observed Therapy (N=20)   - LDV/SOF tablet (LDV 90mg/SOF 400mg) observed daily dosing (modified for non-observed Saturday and Sunday dosing) for 8 weeks   **Group 2:** Unobserved Dosing (N=10)   - LDV/SOF tablet (LDV 90mg/SOF 400mg) provided weekly (7 tablets) for unobserved daily dosing for 8 weeks |
| **Diagnosis and Main Eligibility Criteria:** | Genotype 1, HCV infected, male and non‑pregnant/non‑lactating female subjects, ages 18 years or older, treatment-naïve, and injection drug use in past 30 days.  Reference Section 4.2 and 4.3 of the protocol for detailed Inclusion and Exclusion criteria. |
| - 1. **Study Procedures/ Frequency:** | Screening assessments will be completed across two visits within 10 days of each other and not more than 30 days prior to the enrollment visit.  All subjects will complete the following study visits: screening 1 and 2, enrollment, study visit at weeks 1, 2, 3, 5, 6 and 7, in-depth study visit at weeks 4 and 8, and post-treatment visits at 1, 12 and 36 weeks following the last dose of study drug. For mDOT subjects, there will be additional on-site visits Monday–Friday from enrollment through the week 8 visit for observed dosing.  After consent is obtained and eligibility is determined, screening assessments (split between two visits) will include medical history and physical examination (including weight and height), review of systems, vital signs, concomitant medications, CBC with diff/CMP, PT/INR, HBsAg, HCV RNA, HCV genotype and sub-type (or lab documentation during period of diagnosis of chronic HCV), urine drug screen, HIV Ag/Ab test, and stored sample for potential future.  Enrollment visit will include a urine drug screen, urine β‑hCG (females of childbearing potential only), vital signs, randomization to study arm, motivational interviewing–based counseling pertaining to risk reduction and medication adherence, administration of the Audio Computer Assisted Self Interview (ACASI), and medication dispensation (unobserved dosing) or first directly observed dosing (mDOT).  Study visits (weeks 1, 2, 3, 5, 6, 7) will include directly observed dosing (mDOT) or medication dispensation (unobserved dosing), study drug dosing compliance (pill count), review of concomitant medications and adverse events, urine drug screen, stored samples for potential testing of SOF and LDV metabolite level, and early termination procedures (if applicable). CBC with diff/CMP and HCV RNA will take place at week 2.  Week 4 visit will include all procedures for weekly study visits as well as symptom-driven physical examination, vital signs, ACASI, HCV RNA, and motivational interviewing for medication adherence.  Week 8 visit will include all procedures for weekly study visits as well as symptom-driven physical examination, vital signs, HCV RNA, CBC with diff/CMP, HIV Ag/Ab, ACASI, and a qualitative interview. |
|  | Week 1 post-treatment visit will include review of adverse events, provision of end-of-treatment HCV RNA results, and motivational interviewing–based risk reduction counseling. The rationale for the post-treatment week 1 visit is to inform subjects of their SVR status in person (as opposed to via phone) and provide risk-reduction counseling immediately thereafter. Week 8 is too lengthy to provide SVR status and comprehensive risk-reduction counseling in addition to the other week 8 procedures.  Weeks 12 and 36 post-treatment visits will include review of adverse events, urine drug screen, ACASI, HCV RNA, stored samples for potential HCV RNA sequencing, motivational interviewing-based risk reduction counseling (week 12).  The ACASI, which is administered at enrollment, weeks 4, 8, and post-treatment weeks 12 and 36, will include injection drug use and injection risk behavior, partner-by-partner data on injection/substance use/HCV status, demographic information (enrollment only), drug use history (enrollment only), quality of life scale (EQ5-D), Center for Epidemiologic Studies Depression Rating Scale, and Severity of Dependence Scale and participant satisfaction with treatment (week 8 only). |
| Test Product, Dose, and Mode of Administration: | LDV/SOF is manufactured as a fixed dose combination tablet, consisting of 90 mg LDV and 400 mg SOF, for oral administration. Subjects will take 1 tablet daily with or without food. |
| Reference Therapy, Dose, and Mode of Administration: | mDOT subjects will take 1 tablet daily on-site directly observed by study clinician or specifically trained and authorized study staff. Each Friday, mDOT subjects will receive 2 doses in a WisePill device to be taken Saturday and Sunday unobserved.  Unobserved dosing subjects will receive 7 tablets weekly in a WisePill device to be taken daily unobserved.  Both arms will take 1 tablet orally daily. |
| Criteria for Evaluation |  |
| **Safety:** | AEs and safety laboratory tests will be collected throughout the study (including post-treatment weeks 1, 12 and 36). |
| **Efficacy:** | Efficacy will be evaluated using scheduled assessments of HCV RNA performed using the Roche TaqMan HCV Quantitative Assay. |
| **Pharmacokinetic:** | A single pharmacokinetic (PK) blood sample will be collected and weeks 2, 4, and 8, and early termination (if applicable) for all subjects. PK studies will be run as needed based on end-of-treatment and SVR rates.  The PK of sofosbuvir (and its metabolites GS‑566500 and GS‑331007) and ledipasvir may be assessed. |
| Statistical Methods: | **Aim 1**: To assess the feasibility of treating active PWIDs for HCV with LDV/SOF by mDOT versus unobserved dosing, as measured by recruitment and retention rates overall and by arm. We will calculate the following feasibility measures: 1) proportion of those eligible among those screened; 2) proportion enrolled among those eligible; and 3) study retention and completion rates, overall and by arm. Process measures (e.g., visit length) and reactions to study procedures will also be assessed. Descriptive statistics will be presented with 95% confidence intervals, to help in interpretation. Between-group differences in retention and completion will be assessed using Fisher’s exact and Wilcoxon tests. We will also calculate Kaplan-Meier curves for time to dropout, by group, and test for differences using the log-rank test.  **Aim 2**: To evaluate the acceptability of mDOT versus unobserved dosing, the percent of treatment medication adherence to LDV/SOF, as measured by the percent of doses taken overall (observed and unobserved), will be assessed using DOT doses and weekend Wise Pill data for the mDOT arm, and WisePill data for the unobserved dosing arm. Other outcomes of interest will include completion of therapy, patterns of adherence, and time to stopping medication. Concordance of the various adherence measures will be examined using weighted Kappa and intraclass correlations. Between-arm differences will be assessed using Fisher’s exact and Wilcoxon tests for outcomes measured once, and GEE models for repeated outcomes. We will also use GEE models to compare WisePill openings and pill counts, accounting for between-arm differences in expected frequency.  Sample size justification: The sample will provide typical precision for a pilot study of feasibility and acceptability outcomes. Specifically, we will be able to estimate the mean of continuous outcomes within margins of sampling error (MSEs; half-widths of 95% confidence intervals) of 0.37 standard deviations (SD) overall, and 0.55 SDs within arm; percentages will be estimated within MSEs of 11-18 points overall, and 15-25 points within arm, depending on the sample value. In designing the full-scale trial, these exploratory results will be cautiously interpreted in the light of confidence intervals, plausibility, and prior results.  **Aim 3**: To assess through in-depth, semi-structured qualitative interviews, the challenges with time intensity required for mDOT versus unobserved dosing, and identify key factors affecting treatment adherence for PWIDs treated with LDV/SOF. Transcribed semi-structured interviews conducted at the End-of-Treatment (week 8 or early termination) visit will be imported into Atlas.ti, a qualitative research software program. We will utilize two qualitative analytic methods to interpret data. First, content analysis will allow us to focus on answering study questions regarding experiences with LDV/SOF treatment and DOT strategies, and opinions on challenges to achieving consistent adherence to treatment. *A priori* themes of interest primarily focused on the time-intensity required for this treatment plan and based upon the team’s experience with HCV treatment among PWIDs will be developed and used as the first codebook with which data are coded. Second, thematic analysis with open coding will allow themes to emerge from the data. A coding system will be developed using an iterative process. In the initial phase, we will review all transcripts and field notes to become familiar with the data, and the analytic team will make notes of their observations and potential codes for use in the initial analysis meeting. Then a codebook, consisting of the code definition and inclusion and exclusion criteria, will be created to aid analysis. In addition to predetermined HCV treatment dimensions, additional codes will be developed independently by each analytic team member through an inductive process of identifying themes that emerge from the data. Group analysis meetings will be held to compare independently developed codes for similarity and further definition. A consensus will be reached regarding each code, its application and definition. To ensure consistency, a codebook and dictionary will be developed with universal definitions for each code.  *Inter-rater reliability*: To ensure reliability and validity in the open-ended component of the in-depth interviews analysis, we will implement a verification strategy to ensure self-correction throughout the analysis process. The two coders will assess inter-rater reliability by calculating the correlation between a set of ratings done by two independent raters for the initial set of 3-6 transcripts, and then again on the next set of 6 transcripts. After each inter-rater reliability assessment, the codebook and codes will be revised based on reconciliation of findings done between coders. Inter-rater reliability will be assessed as a team twice during the analysis process and again at the end of analysis as a post-hoc evaluation of reliability and validity. This evolving analysis process will ensure high quality of research decisions, the rationale behind decisions, and the responsiveness of investigators to the data. Once the codebook is developed and verified all remaining transcripts will be coded. Further meetings will be held to discuss any differences in coding and to ensure consistency in the application of codes.  Final analysis will begin with data reduction, then display, analysis and conclusion drawing using a conceptual framework in which hypothesized factors affecting adherence are assessed and unanticipated findings are identified. The analytic team will work from the coded data to merge findings into a final summary and a consensus of major themes, relationships between themes, and ranking of items of most importance to adherence. This method of data reduction encompassing both site and team based analysis creates a robust iterative process through which the data is thoroughly discussed and analytical consensus achieved. *Atlas.ti* software will be used to both code and develop data displays used in the analysis for this study.  **Exploratory Aims**: While we recognize the small sample size limits our ability to draw firm conclusions from exploratory analyses, the paucity of data for this treatment approach allows for hypothesis-generating results.  *End-of-treatment response and SVR*: We will compare the proportion of participants with undetectable HCV RNA at week 8 and post-treatment week 12 between arms using Fisher’s exact tests.  *Acceptability based on drug levels*: If SVR, retention and/or medication adherence data suggestion medication compliance issues, we may compare SOF metabolite–positivity rates will be calculated by week in both arms; between-group differences will be compared using GEE models for repeated outcomes.  *HCV relapse and reinfection*: Among participants who achieve SVR, we will determine the proportion who experience HCV relapse and reinfection at post-treatment week 36, overall and by arm, with exact 95% confidence intervals. We will sequence HCV RNA in such cases to establish if the event represents relapse versus reinfection.  *Social and injection network analyses to inform a subsequent full TasP trial*: We will characterize injector network sizes at baseline and follow-up. Newman’s method will be used to calculate assortativity coefficients, a measure of the degree of demographic and risk behavior similarity within networks. These findings will help us determine whether a full efficacy trial should use targeted sampling strategies to ensure diversity in network sizes, and whether randomization should be stratified by one or both of these factors in future trials.  **Other Exploratory Outcomes**:  *Drug use behaviors before and after HCV treatment*: Recent data suggest significant changes in drug use behaviors after HCV diagnosis: serosorting with other HCV-positive PWIDs and a sustained reduction in drug use. We will assess these behaviors at baseline and follow-up for preliminary estimates of the possible impact of HCV treatment on these behaviors. ANCOVA and conditional logistic models will be used for continuous and binary outcomes respectively.  *Correlates of Adherence and SVR*: We will explore demographic, behavioral correlates of medication adherence using GEE models for repeated measures. In addition, we will explore demographic and behavioral correlates of SVR using Fisher exact tests and exact logistic regression. |

This study will be conducted in accordance with the guidelines of Good Clinical Practices (GCPs) including archiving of essential documents.

GLOSSARY OF ABBREVIATIONS AND DEFINITION OF TERMS

| ° C | degrees Celsius |
| --- | --- |
| ° F | degrees Fahrenheit |
| β-hCG | β-human chorionic gonadotropin |
| ACASI | Audio-Computer Assisted Self Interview Software |
| AE | adverse event |
| ANC | absolute neutrophil count |
| ANCOVA | Analysis of covariance |
| ALT | Alanine transaminase |
| AST | aspartate aminotransferase (also SGOT) |
| BMI | body mass index |
| DSMB | Data safety monitoring board |
| DSMP | Data safety monitoring plan |
| BW | body weight |
| CBC | Complete blood count |
| CDC | Center for Disease Control and Prevention |
| CHR | Committee on human research |
| CI | confidence interval |
| CL_cr_ | creatinine clearance |
| CRF | case report form(s) |
| CMP | Comprehensive metabolic panel |
| CRO | Contract (or clinical) research organization |
| DAA | Direct acting antiviral |
| DAIDS | Division of AIDS Table for Grading the Severity of Adult and Pediatric Adverse Events |
| DOT | Directly observed therapy |
| DSPH | Drug Safety and Public Health |
| EOT | End of Treatment |
| ET | Early Termination |
| FDA | (United States) Food and Drug Administration |
| FDC | Fixed-dose combination |
| GCP | Good Clinical Practice (Guidelines) |
| GEE | Generalized estimating equation |
| GSI | Gilead Sciences, Inc. |
| GT | Genotype (viral) |
| Hb | Hemoglobin |

| HBV | Hepatitis B virus |
| --- | --- |
| HCV | Hepatitis C virus |
| HDPE | High-density polyethylene |
| IB | Investigator Brochure |
| IEC | independent ethics committee |
| IMP | Investigational Medical Product |
| INR | International Normalized Ratio of prothrombin time |
| IRB | institutional review board |
| LDV | Ledipasvir |
| LLN | lower limit of the normal range |
| MCV | mean corpuscular volume or mean cell volume |
| mDOT | Modified directly observed therapy |
| MI | Motivational interviewing |
| min | Minute |
| mmHg | millimeters mercury |
| MSE | Mean squared error |
| PI | Principal investigator |
| PO | per os, by mouth or orally |

| PT | Prothrombin time |
| --- | --- |
| PWID | People who inject drugs |
| QD | once daily (use only in tables) |
| RBC | Red blood cells |
| RBC | red blood cell count |
| SADR | serious adverse drug reaction |
| SAETRS | Serious Events Tracking and Reporting Systems |
| SAMHSA | Substance Abuse and Mental Health Services |
| Scr | serum creatinine |
| SAE | serious adverse event |
| SD | standard deviation |
| SOF | Sofosbuvir |
| SOP | standard operating procedure |
| SUSAR | suspected unexpected serious adverse reaction |
| SVR | sustained virologic response |
| TasP | Treatment as Prevention |
| UCSF | University of California, San Francisco |
| UCLA | University of California, Los Angeles |
| ULN | upper limit of the normal range |
| US | United States |
| VL | Viral load |
| WBC | white blood cells |

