## Study Drug Adherence

mDOT: Subjects will be observed taking LDV/SOF on a daily basis Monday through Friday. Two take-home tablets (doses for Saturday and Sunday) will be dispensed on Friday and will be monitored by the use of a Wise Pill Dispenser, a device currently used in our other trials, which allows for real-time transmission of opening data to estimate medication adherence. Wise Pill Dispensers have been shown to be reliable for real time monitoring of medication adherence, even in resource-limited settings.

Unobserved dosing: Subjects will be provided 7 tablets of LDV/SOF once weekly to take home in a WisePill Dispenser. Medication compliance of study drug will be assessed at every post-enrollment visit through weekly pill counts conducted by study staff. The pill count will take place in the on-site pharmacy and will occur prior to that week’s pill dispensation. If medication compliance is low, study staff will offer basic medication adherence advice to the subject.

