### Enrollment Visit

Enrollment tests and procedures will be completed prior to enrollment and dosing/dispensing of study drug.

Enrollment visit will include a urine drug screen, urine β‑hCG (females of childbearing potential only), vital signs, randomization to study arm, motivational interviewing–based counseling pertaining to risk reduction and medication adherence, administration of the Audio Computer Assisted Self Interview (ACASI), and medication dispensation (unobserved dosing) or first directly observed dosing (mDOT).

Subjects will be randomized 2:1 to mDOT (n=20) or unobserved dosing (n=10) using permuted blocks of randomly selected sizes 2 and 4 generated using a STATA computer program. Staff members who have no contact with study participants will enclose and seal treatment allocation cards in sequentially numbered opaque envelopes to correspond with the randomization sequence. As a participant is enrolled, the envelope that corresponds with their sequence will be opened to reveal their randomized treatment condition.

mDOT subjects will receive a 10-trip Muni card to cover weekly round-trip transportation to study site and the unobserved dosing arm will receive a weekly two-trip Muni card to cover round-trip transportation to study site. These cards will be dispensed at weekly visits only so as to avoid directly compensating participants for attending daily visits.

Subjects will be compensated $20 for the enrollment visit.

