## Data Analysis

### Primary Analysis

### Feasibility: Feasibility of treating active PWIDs for HCV with LDV/SOF by mDOT versus unobserved dosing will be measured by recruitment and retention rates overall and by arm. We will calculate the following feasibility measures: 1) proportion of those eligible among those screened; 2) proportion enrolled among those eligible; and 3) study retention and completion rates, overall and by arm. Process measures (e.g., visit length) and reactions to study procedures will also be assessed. Descriptive statistics will be presented with 95% confidence intervals, to help in interpretation. Between-group differences in retention and completion will be assessed using Fisher’s exact and Wilcoxon tests. We will also calculate Kaplan-Meier curves for time to dropout, by group, and test for differences using the log-rank test.

**Acceptability:** The acceptability of mDOT versus unobserved dosing, the percent of treatment medication adherence to LDV/SOF, will be measured by the percent of doses taken overall (observed and unobserved), will be assessed using DOT doses and weekend WisePill data for the mDOT arm, and WisePill data for the unobserved dosing arm. Other outcomes of interest will include completion of therapy, patterns of adherence, and time to stopping medication. Concordance of the various adherence measures will be examined using weighted Kappa and intraclass correlations. Between-arm differences will be assessed using Fisher’s exact and Wilcoxon tests for outcomes measured once, and GEE models for repeated outcomes. We will also use GEE models to compare WisePill openings and pill counts, accounting for between-arm differences in expected frequency.

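### Weighted kappa and ICC are the only agreement statistics named for the adherence measures, and near-ceiling adherence depresses both even when device error is constant

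*Protocol*

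**What the plan says.** The synopsis (Statistical Methods, Aim 2) and section 9.5.1 (Acceptability) carry the same sentence: "Concordance of the various adherence measures will be examined using weighted Kappa and intraclass correlations". Neither place names percent agreement, a paired difference or limits of agreement. Neither gives the kappa categories or weights, the ICC form, or a cut-off.

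Adherence is measured as percent of doses taken. According to the synopsis it "will be assessed using DOT doses and weekend Wise Pill data for the mDOT arm, and WisePill data for the unobserved dosing arm". Section 9.1.2 lists medication adherence rates among the primary endpoints. The comparator is the pill count. Under Study Drug Adherence, for unobserved dosing: "Medication compliance of study drug will be assessed at every post-enrollment visit through weekly pill counts conducted by study staff". The Weekly Treatment Visits section lists a pill count for the weekly visits without limiting it to one arm.

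Shortly after the concordance sentence, both places add: "We will also use GEE models to compare WisePill openings and pill counts, accounting for between-arm differences in expected frequency". Study Drug Adherence also treats the device as already validated: "Wise Pill Dispensers have been shown to be reliable for real time monitoring of medication adherence, even in resource-limited settings".

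**The concern.** Weighted kappa and the ICC are relative measures. Each sets disagreement between two methods against the spread of the quantity measured. With a once-daily tablet for 8 weeks, adherence may cluster near 100%. A few points of disagreement then weigh heavily against little spread, and both coefficients fall although the device has not become worse. With widely varying adherence the same device looks excellent.

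Neither coefficient reports the direction or size of the gap in percentage points. That gap matters here because WisePill feeds a primary endpoint unequally: nominally all 7 weekly doses in the unobserved arm, but only the 2 weekend doses in the mDOT arm. What is at stake is whether the reported concordance tells the reader anything about the device, or mainly about how varied adherence was.

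**Working it through.** The protocol states no concordance figure, so there is none to reproduce. It also states no expected adherence and no device accuracy. Those inputs are assumptions, shown over a range.

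**Inputs from the protocol.** Enrollment Visit section: 20 mDOT and 10 unobserved. Synopsis: "Subjects will be treated for 8 weeks", one tablet daily. Nominal take-home doses per participant are 8 × 7 = 56 (unobserved) and 8 × 2 = 16 (mDOT weekends).

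**Step 1: daily kappa, exact.** Assume the device is right on 95% of taken and 95% of untaken doses, so raw agreement po is 0.95 at any adherence a. The device records an opening with probability d = 0.95a + 0.05(1 − a). Chance agreement is pe = a·d + (1 − a)(1 − d), and kappa = (po − pe)/(1 − pe).
- a = 0.80: d = 0.770, pe = 0.662, kappa = 0.288/0.338 = 0.85.
- a = 0.98: d = 0.932, pe = 0.9147, kappa = 0.0353/0.0853 = 0.41.

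At a = 0.50, 0.90 and 0.95, kappa is 0.90, 0.76 and 0.63. With 90% accuracy it runs from 0.80 (a = 0.50) to 0.24 (a = 0.98); with 98% accuracy, from 0.96 to 0.65.

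**Step 2: ICC and spread, without bias.** For error SD 4 points and between-person SD s, ICC = s²/(s² + 16).
- s = 20: 400/416 = 0.96.
- s = 5: 25/41 = 0.61.
- s = 3: 9/25 = 0.36.

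The ICC responds to spread. A high mean matters because it compresses the spread.

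**Step 3: the planned statistics at the planned size.** Simulation of 2,000 trials per scenario. Assumptions: person-level adherence beta-distributed, WisePill misses 5% of taken doses, pill count correct. Quadratic-weighted kappa is computed on weekly counts and absolute-agreement ICC on participant percentages; values are simulation means. The expected gap is 5% of mean adherence.

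| Unobserved arm, n = 10 | Kappa | ICC | Gap (points) |
|---|---|---|---|
| Mean 97%, SD 3 | 0.48 | 0.41 | 0.05 × 97 = 4.85 |
| Mean 90%, SD 10 | 0.80 | 0.83 | 0.05 × 90 = 4.5 |
| Mean 80%, SD 20 | 0.92 | 0.96 | 0.05 × 80 = 4.0 |

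Dose-level agreement is 95–96% in all three rows. For mDOT weekend doses (n = 20), kappa runs from 0.51 to 0.89 and ICC from 0.46 to 0.95 across the same scenarios.

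**Step 4: the alternative on the same data.** At mean 97%, SD 3, n = 10, the simulated ICC ranges from 0.04 to 0.79 (2.5th to 97.5th percentile). The paired difference averages −4.8 points with SD 2.8. Its 95% CI half-width is 0.715 × 2.8 = 2.0 points, where 0.715 is t(0.975, 9)/√10. Its limits of agreement are about ±1.96 × 2.8 = ±5.5 points around the mean.

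**Step 5: the denominator.** With an identical device, 16 weekend doses in place of 56 give limits of about ±10.4 points. The wider limits come from fewer doses, not from a worse device.

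**Step 6: why points matter.** If take-home adherence is 97% in both arms and observed doses are recorded without error, a 5% miss rate lowers measured adherence by 4.85 points in the unobserved arm and by 4.85 × 2/7 = 1.4 points in the mDOT arm. A gap in points can be carried into the arm comparison in this way; a kappa cannot.

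**The case against.** Five points can be made for the plan as written.

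- **The GEE comparison is already planned.** A reader might infer that agreement is judged by kappa and ICC alone, and the documents do not support that. If the GEE sentence means one measure against the other, it gives the sign and size of the average gap, and a simple paired comparison of means finds a 4–5 point gap in 99–100% of simulated trials. This stands, but an average gap does not show how far the measures differ for an individual.
- **No verdict on the device is planned.** A reader might infer that a good WisePill could be declared unreliable, or that concordance will decide the adherence measure for the full trial. There is no cut-off or such decision rule, Study Drug Adherence takes reliability as shown, and the Sample Size section promises cautious interpretation. Nor does either passage plan concordance by arm, so a spurious arm difference in measurement quality is not a planned output. This stands.
- **The size rests on assumptions.** At 80% adherence or below the loss is small. This stands.
- **Part of the low ICC is a correct signal.** At mean 97%, SD 3, the bias (4.85 points) exceeds the between-person SD, and a consistency ICC would be about 0.68 rather than about 0.40. This stands in part. The bias is nearly constant across scenarios, so it does not explain the swing from 0.41 to 0.96, and Step 2 shows the same dependence with no bias.
- **Both coefficients are standard, and details can go to an SAP.** Categories, weights and ICC form can. But the protocol does fix the choice of statistics, and that choice is the point here.

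**Conclusion.** The point holds as a cheap improvement to a descriptive, supporting analysis. The named statistics cannot separate device error from low spread in adherence. Under a constant 5% miss rate they roughly double between the near-ceiling and the widely spread scenario (kappa 0.48 to 0.92, ICC 0.41 to 0.96), while the gap stays between 4 and 5 points.

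This rests on assumed device accuracy, a correct pill count, beta-distributed adherence, quadratic weights and the absolute-agreement ICC. It becomes material from about 90–95% adherence upward. The protocol does not say what adherence it expects. Its rationale section does cite an interferon pilot with full compliance, so high adherence is plausible but not established for this regimen.

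The consequence is a concordance result that may mislead its reader. It is not a formal wrong decision about WisePill, and the definition of the primary adherence endpoint is unaffected.

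**What to change.** In section 9.5.1 and in the synopsis under Aim 2, name as the main concordance result the participant-level paired difference in percent of doses: WisePill minus pill count, over the same take-home doses, one value per participant. Report its mean, 95% CI and limits of agreement. Keep weighted kappa and ICC as supportive results.

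Where the difference is shown by arm, state the number of take-home doses per participant (nominally 56 versus 16), and say that wider mDOT limits are not to be read as worse device accuracy.

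No new data are needed. The cost is a few lines of analysis and one more table. With ten participants the limits are themselves imprecise: the standard error of each is roughly √3 × 2.8/√10 = 1.5 points in the near-ceiling scenario. Plotting the individual differences beside them is sensible.
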